**Exclusion criteria**	
1. Pre-injury psychiatric or neurological disease by self-report (e.g., anxiety disorder, ADHD, Parkinson’s disease, etc.) 2. History of diagnosed severe depression (diagnosed pre-injury) 3. History of epilepsy (diagnosed pre-injury) 4. Family history of epilepsy 5. Have had fainting spells or syncope in the last 3 years pre-injury 6. Have significant hearing loss, vision or motor impairment that would prevent them from performing the task 7. Known to be pregnant 8. Consuming medication affecting cortical excitability or recreational drugs^a^ 9. Metal (except titanium) or electronic implants in the brain /skull (e.g., splinters, fragments, clips, cochlear implant, deep brain stimulation, medication pump…) 10. Metal (except titanium) or any electronic device at other sites in your body, such as cardiac pacemaker or traumatic metallic residual fragments 11. Have skin problems such as dermatitis, psoriasis or eczema under the stimulation sites 12. Have had brain stimulation in the past 6 months 13. Have undergone transcranial electric or magnetic stimulation in the past (more than 6 months) which resulted in adverse effects 14. Skull fractures, significant skull defects, skull plates or large vessels occlusions, no significant cortical lesion or atrophy at the site of electrode 15. Having had a seizure at the time of accident or between the injury and starting of the therapy.	

^a^We follow recommendations by McLaren et al. [49], and only exclude drugs that are shown to block tDCS effects (e.g., sodium channel blockers, calcium channel blockers, and NMDA receptor antagonist), while other medications shown to only modulate tDCS effects will be tracked and considered as covariate in the analysis. We will monitor for medication changes as a potential bias on the outcomes of the intervention and report any changes that may occur. If a patient become in need of medications shown to block tDCS effects, they will be excluded from further participation. We will monitor changes in medication and general health through in-person briefing during the first 2 weeks of the intervention, when a researcher is visiting the patient’s house, and via phone calls (e.g. “Have there been any changes in your health or medications since our last phone call?”) during the remaining 3 weeks of the intervention

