#### Randomization and blinding

A computer programme will generate forty random flags identifying the patient’s group (20 flags equal to 1 for ACTIVE, 20 flags equal to 0 for SHAM). Flag order will then be shuffled and a participant’s unique ID (sub-01, sub-02, … sub-40) associated to a flag, following the order of attendance. The study design is double blind: participants and the assessors will not know until the end of the intervention if the participant had received active or sham brain stimulation. A member of the research team (not the assessor) will program two stimulation protocols (active and sham) on the stimulation device, which will be set to operate into blind mode. As such, the person who administers the stimulation will be blind to the details of the protocol. Meaning they will not be able to see the details of the protocol. Patients are then randomly assigned to one or the other protocol, resulting in an intervention blind both to the assessor and the patient.

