##### Outcome assessment (T4)

A final follow-up assessment, identical to the one at T2 and T3, will be carried out 1 month after the completion of the intervention, to assess maintenance of working memory improvements and transfer.

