#### Cognitive tasks and questionnaires

A series of cognitive tasks will be administered at different time points and for a different purpose during the study: *screening*, *training*, and *outcome assessment*.
Screening: the Digit Span, Arithmetic, Symbol Span, and Spatial Addition subtests from the WAIS-IV and WMS-IV will be used for screening participants for cognitive impairment (see 3.5.4, 35 min to complete). A description of the task is given in Table 3.Training Task: The visuo-spatial training task is a visuo-spatial adaptive n-back (see section 3.5.3).Outcome: 1) the Dalhousie Computerized Attention Battery (DalCAB, [68], 35 min to complete) will be used as the outcome assessment battery. A description of the tasks in the battery is provided in Table 4. For a detailed description of the parameters used in each task see [68]; 2) In addition, a non-adaptive visuo-spatial N-back task will also be used as outcome measure, with fixed levels of *N* = 1,2,3. (~ 30 min to complete); 3) The Digit span, Arithmetic span, Symbol span and spatial addition will also be used as outcome measures.A series of questionnaires and feedback forms will also be administered at single or multiple time points throughout the intervention to record variables that may impact or may be affected by performance on the task. Permission to use these instruments has been obtained for those questionnaires requiring it. A list of the questionnaires, together with a brief explanation and references is presented in Table 5.

**Table 5 Tab5:** Questionnaires

	Questionnaire	Taken at
*Individual lifestyle*	Participant Health History (including details on injury, medications etc..)	T1
	Epworth Sleepiness Scale (to report habitual sleepiness [62]	
	Quality of life assessment (The Whoqol Group [63]), − in four facets (Physical health, Psychological, Social relationships, Environment)	
*Individual cognitive state*	Cognitive Failures Questionnaire (CFQ, [64]) to measure self-reported failures in perception, memory, and motor function.	T1
	Hospital Anxiety and Depression Scale (HADS) to measure emotional symptoms (HADS; [65])	
	Patient Reported Evaluation of Cognitive Status (PRECiS [66];)	T1/T3/T4
*Feedback on the of intervention*	Side effect of the tCS [57]	Every tCS session
	System usability scale (SUS [67];)	T3
	Attitude towards stimulation (to record how they feel their attitude towards the brain stimulation affected performance)	

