	Feedback on strategy (to record whether they use a specific strategy to complete the training task)	
	Blinding questionnaire (to confirm efficacy of the blinding procedure)	T4

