#### Outcome measures

Our primary outcome measure will be the training gain*,* obtained by looking at the relative change in n-level (# items maintained in working memory) over the course of the training, as well as performance increments in the pre−/post-test outcome measures in the stimulation relative to the control (SHAM) group. Transfer of improvement to other cognitive domains will be assessed by comparing performance in a battery of cognitive tasks given at different times points throughout and after the intervention. Maintenance of improvement will be assessed by comparing outcome measures (Table 4) at different occasions during and after the conclusion of the study.
Training gain. Performance in training is measured as the N level reached on every session. The training gain is defined as the difference in N levels at two time points. Accuracies and reaction times at trial level will also be collected. In addition, we will administer a non-adaptive visuo-spatial task (N = 1, *N* = 2, *N* = 3), to allow us to quantify improvements at different testing points in terms of accuracy and reaction times in the trained cognitive domain.Transfer. We will use spatial tasks that test the same cognitive process as the training task to evaluate transfer to closely related tasks. We will use the same spatial addition and the symbol span task also used in the screening phase. We also will use the Dalhousie Computerized Attention Battery (DalCAB) [68], 8 cognitive tests to assess attentional functions in the vigilance, orienting and executive control attention network. Tasks are described in Table 4. Reaction time and accuracy will be computed for each task.Maintenance. To identify how long benefits of training and or stimulation are maintained in time, we will compare changes between outcome measures at T3 and at T4, 1 month after the end of the intervention.Everyday life improvement. It is important to understand whether improvement in cognitive tasks targeting specific processes can transfer to improvement in everyday life activities. We will use a self-reported questionnaire (PRECIS, Patchick et al., Clinical Rehabilitation, [66]) to evaluate if and how training in cognitive tasks targeting specific processes impacts on everyday activities.

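### The stated blind ends with the 5-week intervention, about a month before T4, and the only blinding check is at T4

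*Protocol article*

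**What the plan says.** All references are to the protocol article.

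- **Length of the blind.** Randomization and blinding states that "participants and the assessors will not know until the end of the intervention if the participant had received active or sham brain stimulation". No other section extends the blind to T4 or to database lock.
- **Meaning of intervention.** The footnote to Table 1 describes health and medication checks made in person in the first 2 weeks and by telephone "during the remaining 3 weeks of the intervention". The follow-up month is not counted.
- **Timing and use of T4.** Outcome assessment (T4) says the visit "will be carried out 1 month after the completion of the intervention". For maintenance, Outcome measures says "we will compare changes between outcome measures at T3 and at T4, 1 month after the end of the intervention".
- **Blinding check.** Table 5 has the entry "Blinding questionnaire (to confirm efficacy of the blinding procedure"), with T4 as its only time point.
- **Device set-up.** A team member other than the assessor "will program two stimulation protocols (active and sham) on the stimulation device, which will be set to operate into blind mode". Each patient is assigned to one of these two. Under Eligibility criteria, the assessors also give the stimulation.

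**The concern.** The trial describes itself as assessor- and patient-blinded, yet the one sentence that says how long the blind lasts stops it before the final visit. Prolonging benefit to 1 month is a key secondary objective, and it rests on the change from T3 to T4. A blind that may be lifted between those two visits may be lifted inside the contrast itself.

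The T4 measures most open to expectation are PRECiS, which is self-rated and is the article's measure of everyday-life improvement, and the WAIS-IV/WMS-IV subtests, which an examiner delivers in person. If patients or assessors knew the arm by then, a group difference at T4 could not be separated from expectation, and no analysis could repair it.

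The check on blinding has a related weakness. It is asked once, long after the last stimulation session and at a time when allocation may already have been disclosed.

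**Working it through.** The article gives no figure to reproduce here, so the check sets the passages side by side.

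**1. When the stated blind ends.**

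| Event | Source | Time from first session |
|---|---|---|
| Session 10, last stimulation | Training phase 1 | end of week 2 |
| T2 | Outcome assessment (T2) | after session 10 |
| End of training alone | Training phase 2 | 2 + 3 = 5 weeks |
| T3 | Outcome assessment (T3) | on completion of training |
| T4 | Outcome assessment (T4) | 5 weeks + 1 month |

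The Table 1 footnote counts the 3 weeks of training alone as the rest of the intervention. The T4 section and the maintenance paragraph both place T4 one month after the intervention is over. Outcome measures also separates testing during the intervention from testing after it. On that usage the blind in Randomization and blinding lapses at about week 5. T3 sits at the boundary and is taken here as inside the blind. T4 is outside it.

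**2. What is exposed at T4.** Table 5 gives PRECiS at T1, T3 and T4. T4 is described as identical to T2 and T3, and T2 includes the WAIS-IV/WMS-IV subtests. Table 3 shows that these are read or presented to the patient. The T1 section says the assessor is blind to group; the T4 section says nothing on this.

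**3. Delay of the blinding question.** Session 10 to T4 = 3 weeks + 1 month, or about 7 weeks. This holds however the word intervention is read.

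**4. Conditional point on the two stored protocols.** Suppose an assessor can tell which of the two protocols is run for each patient, and the labels keep their meaning throughout. There are then only 2 possible keys, and one disclosure leaves 1, so the arm of every patient that assessor has stimulated is known. With participant-specific codes and a 20/20 allocation, one disclosure would leave 39 patients, 20 of them in the other arm. The best guess for any one of them would be right with probability 20/39 = 51.3%. The article states neither supposition. It says that blind mode hides the details of the protocol, but not whether it hides which one is run. It describes no participant-specific code.

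**The case against.** **No unblinding is scheduled.** The sentence sets a minimum period of blindness. It does not say that anyone is told their arm before T4, and the trial is elsewhere called assessor- and patient-blinded without a time limit. This stands, and it limits the finding to what the text permits. A reader might infer that T4 will be open-label; the article does not say so.

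**The word intervention is used loosely.** The Abstract lists the 1-month visit among time points during the intervention, and Cognitive tasks and questionnaires speaks similarly of forms that include some at T4. A blinding questionnaire at T4 also makes most sense if participants are still blind. This makes the narrow reading less certain. But the three sections that define the schedule use the narrow sense, and nothing extends the blind to T4.

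**Much of the outcome set is protected.** The adaptive n-level is recorded by computer during training, before each participant's own end of intervention. The DalCAB and fixed n-back are computerised. This stands: the direct exposure is mainly PRECiS and the four subtests at T4.

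**The questionnaire still has value.** If participants had been told their arm, nearly all would answer correctly, and that would show. Side effects are also recorded at every stimulation session. Both points are fair, but neither makes a question asked 7 weeks late a good test of the sham.

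**A stronger reading is tempting.** Because all patients share two stored protocols, a reader might infer that one disclosure breaks the code for all 39 others and unblinds every later visit from T1 on. The documents do not support that. It needs individual disclosure while recruitment continues, an assessor who can tell the protocols apart, fixed labels, and the same assessor throughout. The article states none of these and refers to assessors in the plural. T1 also precedes a patient's first stimulation session, so no protocol run has yet shown the assessor that patient's arm.

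**Conclusion.** The concern holds in two parts.

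- **Length of the blind.** As written, it ends about a month before T4. The T3-to-T4 maintenance contrast, the T4 PRECiS, the T4 examiner-delivered subtests and the blinding questionnaire all fall outside it, for up to 40 participants. This rests on the narrow sense of intervention, which the operative sections support and the Abstract blurs. It is a permission in the text, not a scheduled unblinding.
- **Timing of the blinding check.** The questionnaire comes about 7 weeks after the last stimulation session. It is a poor check of the sham whether or not the blind holds. This rests on Table 5.

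The shared-protocol route is conditional only. If assessors can tell which protocol is run and the labels stay fixed, a disclosure during recruitment could reveal the arm of other patients stimulated by that assessor. The article does not establish either condition.

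**What to change.** 1. In Randomization and blinding, state that allocation is withheld from participants and assessors until the last participant's T4 is complete and the database is locked.
2. In Table 5, and in Table 2 if it shows the same timing, move the blinding question to right after session 10, before T2 testing. A repeat at T4 is optional.
3. Optional extra safeguard: have the team member who already programs the device store the stimulation under participant-specific codes. The first change already closes this route for planned disclosures; the codes would limit the effect of an accidental one.

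The first two changes cost protocol wording and one form moved to an existing point of contact. They add no visit and leave the sample size and the treatment as they are. The one small downside is that early participants wait longer to learn their allocation.

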#### Brain stimulation protocol

Brain stimulation will be administered using a Starstim 8 brain stimulation device (Neuroelectrics®). Standardized locations derived from electroencephalography will be used to place the electrodes over the right dorsolateral prefrontal cortex (DLPFC). We will use a bipolar setup, includes two circular Ag/AgCl electrodes (area = 3.14 cm^2^) filled with conductive gel and placed on F4 (anode) and Fp1 (cathode). Reference electrodes will be attached to the earlobe and impedances will be measured throughout the stimulation and kept below 20 kΩ. We will use a total current intensity of 2 mA for 20 min, preceded by 30 s ramping up and followed by 30 s ramping down (total stimulation time = 21 s). With these parameters and Ag/AgCl electrodes (area of 3.14 cm^2^) we obtain a current density of approximately 0.6 mA/cm^2, slightly higher than the one obtained with larger electrodes, but still well below the threshold for risk of tissue damage [57–59]. The simulated current distribution obtained with such setup is shown in Fig. 1. During sham stimulation, we will use the same setup as in the active condition but after ramping up, the current will be brought back to zero and the ramp up/down process repeated 30 s before the end of the 21 min time interval (total sham stimulation time = 21 min). We have recently completed data collection with the same protocol in 28 elderly and another study on stroke patients is undergoing: in these participants, brain stimulation has been well received.

**Fig. 1 Fig1:**
[figure not shown]
Frontal view of the simulated electric field (normal component (En) with tDCS configuration used in the study. The simulated electric field was obtained with StimViewer (Neuroelectrics®), using the realistic head model described in Miranda et al. [60]. Briefly, tissue boundaries were derived from MR images (scalp, skull, cerebrospinal fluid (CSF) – including ventricles, grey matter and white matter) and the Finite Element Method was used to calculate the electric potential in the head, with circular electrodes with a 3.14 cm^2^ area. Tissues were assumed to be uniform and isotropic and values for their electric conductivity were taken from the literature. A positive value for the component of the electric field normal to the cortical surface means the electric field normal component is pointing into the cortex, and such a field would be excitatory. On the other hand, an electric field pointing out of the cortex (negative normal component) would be inhibitory. Details of the simulation parameters are taken from https://www.neuroelectrics.com/wiki/index.php/Simulating_tCS_Electric_Fields_in_the_Brain

#### Working memory training

The working memory training task is an internet-based visuo-spatial adaptive n-back training program. The same training paradigm has recently been successfully used with stroke patients [61]. Players must attend to a visual stream of spatial information that is presented sequentially and look for matches. Participants will see a grid with eight spaces, with one space filled in on each trial and they will press a button upon seeing a “match” in position with ‘n’ trials before. Within each session, players begin at a level of *n* = 1 and can progress up to *n* = 6 based on their scores in the previous block (i.e., this program is adaptive (closely following Jaeggi et al. [24]). Each session consists of 20 blocks of 20 + n trials each (~ 1 min per block), and progression to the next block is self-paced by the participant. This training task will last for ~ 20 min.

#### Participants’ timeline

The flowchart of the procedure is shown in Fig. 2, while a schedule of enrolment, interventions, and assessments is shown in Table 2. The care team as part of the research team identifies potential participants during the cognitive assessment, which is part of the routine care, and invites them to participate. Patients expressing an interest in the study are made aware of possible side effects of brain stimulation and asked to confirm their willingness to participate. During the first in-lab session (T0), following the informed consent procedure, each participant is randomly assigned to one of the two groups (active or sham stimulation) and interviewed by the assessor with a screening questionnaire, including questions about demographic information and health history to evaluate the inclusion/exclusion criteria. We also record information about current medications and information about time since injury, handedness and colour blindness. At this point, participants who don’t meet the eligibility criteria are excluded from further participation.

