### Eligibility criteria

The study will recruit patients who experienced an ABI and have been referred to the Community Brian Injury Service of NHFT. Patients provide written, informed consent before any study procedure occurs (see Fig. 2) and must meet eligibility criteria (Table 1) at randomization. Assessors, who will also administer the brain stimulation, will receive training in the use of tDCS and basic life support.

**Table 1 Tab1:** Eligibility criteria

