##### Outcome assessment (T1)

On the following day participants perform a series of pre-training outcome tasks (T1; Table 4), administered by an assessor, to measure their baseline working memory capacity and to assess, during and at the end of the training intervention, the efficacy of the training and the stimulation regime. These tests will not be used to determine eligibility. The assessor is blind to group assignment (control vs active).

On the same day as T1 testing, the assessor will familiarize them with the stimulation procedure (which is identical for sham or active) and the training game. The member of the team administering the training answers any questions about the study. Overall, this second session lasts for about 1 h.

##### Training phase 1

On the 10 consecutive training days after the T1 session, depending on the group, participants will receive active or sham brain stimulation (see section 3.5.2). As the assessor, who administer brain stimulation, is blind to the intervention, the procedure will be the same for both groups. At the same time, both groups complete the working memory training exercise for 20 min. If the WM training finishes before the stimulation, participants are asked to wait until the end of the tDCS session (20 min). Before each training session, participants are also asked to answer short questions (level of alertness, engagement, etc.). Once the training session and the stimulation are complete, the participant fills in a feedback form on the side effects of brain stimulation experienced, if any.

Participants will complete 10 consecutive training sessions (2 weeks, excluding weekends. Each session should take about 45 min (~ 10 min setting up of tDCS and ~ 20 min of WM training). This phase will be completed at home, with the assistance of the trainer. An attempt will be made to start the intervention on a Monday, therefore aiming to have breaks in the stimulation at the same point in the 2 weeks, and to keep the training time consistent over days. Nevertheless, administration time and date will be recorded. By the end of these 10 sessions, participants will be familiar with the training game and will be able to confidently undertake the training by themselves in the next 15 sessions.

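### The timeline assigns patients to a group before the interview that checks eligibility, contradicting the eligibility section and leaving the 40 allocations exposed to loss

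*Protocol article*

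**What the plan says.** Three sections of the protocol article bear on the order of events.

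- **Participants' timeline.** At the T0 visit, once consent is given, "each participant is randomly assigned to one of the two groups (active or sham stimulation) and interviewed by the assessor with a screening questionnaire". That questionnaire is described as "including questions about demographic information and health history to evaluate the inclusion/exclusion criteria". The paragraph ends by saying that, at that stage, participants "who don’t meet the eligibility criteria are excluded from further participation".
- **Eligibility criteria.** Patients consent before any study procedure and "must meet eligibility criteria (Table 1) at randomization".
- **Randomization and blinding.** A program generates a fixed set of forty flags ("20 flags equal to 1 for ACTIVE, 20 flags equal to 0 for SHAM") and shuffles them. IDs sub-01 to sub-40 are linked to the flags in the order in which patients attend.

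The Recruitment section plans for forty adults. The Baseline session section gives the T0 measures to eligible participants only, so the exclusion falls after assignment but before baseline testing. The T1 section places the first outcome tests a day later: "On the following day participants perform a series of pre-training outcome tasks".

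**The concern.** The timeline describes assign, then interview, then exclude. The eligibility section requires the criteria to be satisfied when assignment takes place. A site that follows the timeline cannot guarantee the eligibility rule.

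Three things are at stake:

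1. **The allocation list.** It has no spare places. A patient who takes a flag at T0 and then fails the interview leaves one flag fewer for an eligible patient.
2. **The balance.** The 20:20 split holds over all forty flags. It need not hold over the subset that remains after exclusions.
3. **The analysis set.** A person assigned and then found ineligible has been randomised. The article does not say whether that person belongs to the randomised population.

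The sample size section computes about 48 and settles for 40, so the plan has no margin for lost places.

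**Working it through.** **Step 1. Order of events.**

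| Section | Order described |
|---|---|
| Eligibility criteria | Criteria met, then randomisation |
| Participants' timeline | Consent, assignment, eligibility interview, exclusion of those who fail |
| Baseline session | Baseline measures for eligible participants, after consent |

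The first two rows conflict. The third fits either order.

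**Step 2. What is still open at T0.** Under Recruitment, the FSIQ and working-memory index scores come from routine care, and under Participants' timeline potential participants are identified at that assessment. These criteria are therefore largely settled before T0. The health-history and medication items are evaluated at the T0 interview. Table 1 lists 15 exclusions, among them family history of epilepsy, implants, medication and seizure since injury. The timeline itself provides for some patients failing.

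**Step 3. The plan's own figure.** Inputs from Sample size calculation: effect size d = 0.73, alpha 0.05, power 0.80, N about 48, planned N = 40. For a two-sample t-test with n per arm, power is taken from the noncentral t distribution with 2n − 2 degrees of freedom and noncentrality d × √(n/2).

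- One-sided, n = 24 per arm (N = 48): noncentrality 0.73 × √12 = 2.53, power 0.801. The stated 48 is reproduced.
- Two-sided, 80% power needs N = 62, so 48 reproduces only as one-sided. The article does not state sidedness, so both are shown below. Sidedness, and the choice of 40 over 48, are separate matters.

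**Step 4. Effect of lost flags on power.** The failure rate f is not stated; 10% and 20% are assumptions. Without replacement, the number remaining is 40 × (1 − f).

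| Assumed f | Remaining | n per arm if equal | Noncentrality | Power, one-sided | Power, two-sided |
|---|---|---|---|---|---|
| 0% | 40 | 20 | 0.73 × √10 = 2.31 | 73.3% | 61.4% |
| 10% | 36 | 18 | 0.73 × √9 = 2.19 | 69.2% | 56.7% |
| 20% | 32 | 16 | 0.73 × √8 = 2.06 | 64.5% | 51.5% |

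These rows assume equal arms. Allowing for random losses between the arms lowers the last row slightly, to about 64% and 51%. To fill 40 eligible places, 40 / (1 − f) patients would have to be assigned: 45 at 10% and 50 at 20%. Only 40 flags exist.

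**Step 5. Effect on balance.** If k of the 40 flags are lost at random, the number lost from the active arm is hypergeometric, and the arms differ by |k − 2x| when x active flags are lost.

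- k = 4 (10%): P(equal arms) = C(20,2)² / C(40,4) = 36,100 / 91,390 = 0.40; P(difference of 4 or more) = 0.11.
- k = 8 (20%): P(equal arms) = C(20,4)² / C(40,8) = 23,474,025 / 76,904,685 = 0.31; P(difference of 4 or more) = 0.24.

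The power cost of imbalance itself is small. Arms of 20 and 16 give 68.7% one-sided, against 69.2% for 18 and 18. Almost all of the loss comes from the smaller total.

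**The case against.** **Loose drafting.** The timeline joins assignment and interview with a plain conjunction, and it refers to a flowchart and a schedule that are not reproduced in the text available. The eligibility section states the usual rule. One badly ordered sentence is a real possibility. This stands as a limit on what can be said about intended practice, but not as a defence of the text: the printed order conflicts with the eligibility section, and a correct flowchart would leave that conflict in place.

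**Flag loss is inferred.** The article does not say that a patient who fails the interview keeps an ID, and a replacement rule may sit in the fuller protocol. This also stands in part. The loss is the direct reading of assignment at T0, flags taken by order of attendance and IDs ending at sub-40. It is not stated outright.

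**Bias.** A reader might infer that excluding patients after assignment means the compared groups are no longer the randomised ones, and so are biased. The article does not support that. The interviewing assessor is described as blind to group, the exclusions rest on facts that predate assignment, and they occur before any stimulation. Exclusion on those terms should not depend on arm.

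**T1 after assignment.** A reader might also treat the T1 tests, done a day after assignment, as an error. Nothing in the article makes them one: patient and assessor are both described as blind, and loss of patients in that one-day gap is conjecture. A patient who left then would lack a pre-test value, but training gain is computed from levels reached in the training sessions.

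**Size.** The failure rates have no source in the article, and the core cognitive criteria are screened earlier, so the true rate could be low. This stands, and the figures are illustrations only.

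**Conclusion.** The point holds as an explicit contradiction between the Eligibility criteria and Participants' timeline sections. With a closed list of 40 flags and no replacement rule shown, following the timeline as printed can use up allocations on ineligible patients. Forty eligible patients and a 20:20 split are then not assured, and the analysis status of randomised-but-ineligible patients is left open.

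The size depends on an unstated failure rate. At an assumed 10% to 20% without replacement, 4 to 8 places are lost. The power cost is about 4 to 9 percentage points one-sided, or 5 to 10 two-sided, at d = 0.73. If excluded patients are replaced from further allocations, most of that cost disappears. The contradiction does not depend on these assumptions. The finding is about order, lost places and an undefined analysis status; it does not show a biased comparison.

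**What to change.** Reorder the Participants' timeline paragraph so that consent and the eligibility interview are completed, and eligibility is confirmed, before the next flag and ID are released. Give list IDs only to patients confirmed eligible. Align the flowchart if it shows the other order.

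Add one sentence saying how anyone found ineligible after assignment is counted in the analysis, and whether that allocation is replaced.

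The cost is a change of wording. The same steps are carried out by the same people, and the list of 40 can stay as it is.

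As an optional refinement, the flag could be released after the T1 tests and before the first stimulation session. Familiarisation at T1 is described as the same for both groups, so nothing before that session needs the allocation. This would give every randomised patient a pre-training value at no cost, but the contradiction does not require it.
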